### Participants and selection criteria

Participants will be students from the University of Granada (Granada, Spain). The University of Granada has  $\approx 65,000$  graduate students, of which  $\approx 40,000$  are 18-25 years. Eligible participants should be 18-25 years old and should have a body mass index (BMI) between 18.5 to 35 kg/m^2. The inclusion and exclusion criteria are listed in Table 1. We decided to implement the intervention on young adults with a wide range of BMI because overweight and obesity at this age is associated with an increased risk of cardiovascular disease among future middle-aged adults [39]. Moreover, BAT seems to be related to age and BMI [9, 40], being higher in younger and thinner people. Thus, people aged 18-25 years old are expected to present detectable BAT activity and mass [10, 41]. Further, persons of this age are legally able to sign themselves informed consent to participate in ACTIBATE, and no ethical issues are raised due to participant's age and type of measurements to be undertaken in the study. Risks will be minimized by ruling out contraindications to the testing and training protocols via a health history and a thorough physical examination prior to the testing sessions. If any medical problems arise during the project, participants will be referred for medical evaluation and, if necessary, dropped from the study. ACTIBATE has subscribed private liability insurance covering participants, investigator's responsibility as well as the responsibility of any person involved in the study, provided that there is proper adherence to the protocol.

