- **White adipose tissue and muscle biopsies.** To analyse the expression of genes encoding proteins involved in the thermogenic machinery, mitochondriogenesis and Brite brown adipocytes, we will obtain biopsies from abdominal subcutaneous white adipose tissue at the umbilical level to quantify whether there exists browning in white adipose tissue depots, expression of UCP-1 and other potential targets involved in the browning process; and in skeletal muscle at *vastus lateralis* to quantify the expression of genes encoding proteins potentially involved in human thermogenesis. An expert surgeon will perform the biopsies following the Bergström's technique. Immunohistochemical staining and quantitative RT-PCR will be used to perform these analyses.
- **Plasma samples and biochemical analysis.** We will also measure a full set of cardiovascular risk factors including fasting plasma lipids and lipoproteins, glucose and insulin, myeloperoxidase, e-selectin, vessel cell adhesive protein 1, and immunoglobulin cell adhesive protein, cytokines (e.g tumor necrosis factor alpha, IL-6 and monocyte chemotactic protein 1) adipokines (e.g leptin, adiponectin, resistin and active plasminogen activation inhibitor factor 1) as well as irisin and soluble (extracellular) FNDC5, orexin A and B neuropeptides, atrial natriuretic peptides, bone morphogenetic protein 7, fibroblast growth factor 21, transforming growth factor- $\beta$ , and  $\beta$ -aminoisobutyric acid, among others. ELISA kits, western blots and High Performance Liquid Chromatography- Mass Spectroscopy will be used to perform these analyses.
- **Cardiorespiratory fitness.** It will be determined using a maximum treadmill exercise test (h/p cosmos, Italy) following the modified Balke protocol [66], which has been extensively used and validated [67-69]. The criteria for achieving maximum oxygen consumption ( $VO_{2max}$ ) will be: respiratory exchange ratio  $\geq 1.1$ , a plateau in  $VO_2$  (change of  $<100$  ml/min in the last three consecutive 10 seconds stage), and a heart rate within 10 beats/min of the age-predicted maximal heart rate ( $209-0.73 \times \text{age}$ ). Participants that do not achieve these criteria will be classified as having reached the  $VO_{2peak}$ . Subsequent analysis will account for this factor. The exercise electrocardiogram will be monitored continuously.

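### The heart-rate criterion for VO2max is two-sided as written, so a test more than 10 beats/min above the age prediction is labelled VO2peak even when the other criteria are met

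*Protocol*

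**What the plan says.** The cardiorespiratory fitness item under Secondary outcomes in the Protocol sets three criteria for VO2max and joins them with 'and':

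- a "respiratory exchange ratio" of at least 1.1;
- a plateau, defined as a change in oxygen uptake below 100 "ml/min in the last three consecutive 10 seconds stage";
- "a heart rate within 10 beats/min of the age-predicted maximal heart rate", where the prediction is 209 − 0.73 × age.

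On failure, the rule reads "Participants that do not achieve these criteria will be classified as having reached the" VO2peak. It is followed by "Subsequent analysis will account for this factor", without a method.

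The section on participants and selection criteria fixes the age range: "Eligible participants should be 18-25 years old". Table 2 schedules the test at baseline and weeks 8, 16 and 25. The Outcomes measures section places cardiorespiratory fitness among the further variables rather than among the secondary outcomes it names, although Table 2 and the Secondary outcomes section list it there.

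**The concern.** The purpose of the heart-rate criterion is to screen out tests that stopped short of a maximal effort. A heart rate well below the prediction is evidence of that; a heart rate well above it is not. The wording nevertheless sets a limit on both sides. Because all three criteria must be met, exceeding the upper limit is enough by itself to change the label.

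At stake is the VO2max/VO2peak label, which the protocol says the analysis will take into account. An analyst who codes the rule as printed would put some maximal tests in the VO2peak category because their heart rate was too high. The same could happen at any of the four visits.

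**Working it through.** The protocol states no figure for how often the rule misclassifies, so there is none to reproduce. The check evaluates the rule as printed and then asks how many maximal tests the upper limit could catch.

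**Step 1. The band.** Inputs from the Protocol: predicted maximum = 209 − 0.73 × age; tolerance 10 beats/min; ages 18 to 25.

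| Age | Predicted | Lower limit | Upper limit |
|---|---|---|---|
| 18 | 209 − 13.14 = 195.86 | 185.86 | 205.86 |
| 20 | 209 − 14.60 = 194.40 | 184.40 | 204.40 |
| 25 | 209 − 18.25 = 190.75 | 180.75 | 200.75 |

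A 20-year-old who reaches 206 beats/min with a plateau and a sufficient respiratory exchange ratio exceeds 204.4 and is labelled VO2peak. The same participant at 204 would be labelled VO2max.

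**Step 2. How often the upper limit is crossed.** The protocol does not give the spread of true maximal heart rate around the prediction. Assume it is normal with mean error zero and SD s. The share of maximal tests above the band is 1 − Φ(10/s).

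| Assumed s (beats/min) | 10/s | Share above the band | Of 150 participants at one visit |
|---|---|---|---|
| 5 | 2.00 | 2.3% | 3.4 |
| 7 | 1.43 | 7.7% | 11.5 |
| 10 | 1.00 | 15.9% | 23.8 |
| 12 | 0.83 | 20.2% | 30.3 |

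The last column takes every one of the 150 planned participants as tested and maximal, so it is a ceiling for each s.

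These are shares missing the heart-rate criterion on the high side. The share whose label turns on that alone is smaller, because some of these tests will also miss another criterion. As an illustration, suppose 53.4% of true plateaus pass the plateau check (a simulated figure that assumes 10-second noise with SD 60 ml/min), every test passes on respiratory exchange ratio, and the criteria are independent. Then s = 7, 10 and 12 give 0.077 × 0.534 = 4.1%, 0.159 × 0.534 = 8.5% and 0.202 × 0.534 = 10.8%.

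**Step 3. What a one-sided rule changes.** With only the lower limit, the thresholds are 185.86 (age 18) down to 180.75 (age 25), and nobody fails for a high heart rate. Under the symmetric assumption in step 2, the same share of maximal tests still falls below the lower limit. The change therefore removes the upper-side failures and no others.

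**Step 4. The plateau limit, as a secondary remark.** For a straight-line rise with no plateau, the change is slope × span. It stays under 100 ml/min if the slope is below 300 ml/min per minute over 20 s (100 × 60/20) or below 200 over 30 s (100 × 60/30). The text "in the last three consecutive 10 seconds stage" allows either span, depending on whether the stages are measured start to start or end to end. The test is run "following the modified Balke protocol", but the protocol gives neither its speed and grade steps nor the rate at which oxygen uptake rises. With the protocol's own 3.5 ml/kg/min per MET and its 90 kg example participant, a rise of 0.5 MET per minute gives 52.5 ml/min over 20 s and 78.8 over 30 s, both within the limit. A rise of 1 MET per minute gives 105 and 157.5, both outside it.

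**The case against.** The strongest reply is that a lower bound was plainly meant and that trained staff would apply it that way. That is probably right about intent, but the text does not say so, and an upper limit on heart rate serves no evident purpose here.

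Several limits on the point stand in full:

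- A reader might infer that anyone exceeding the prediction fails. That is not so: up to 10 beats/min above it passes.
- A reader might infer that tests are discarded or called submaximal. The protocol only relabels them as VO2peak; the measured value is kept.
- A reader might infer that the plateau limit is always met by a test with no plateau. That depends on a rate of rise the protocol does not give. For example, an assumed 3 ml/kg/min per minute at 90 kg is 270 ml/min per minute, which gives 90 ml/min over 20 s but 135 over 30 s.
- A reader might infer that the label as a whole fails to separate maximal from other tests. The criteria are joined by 'and', so a false plateau alone does not yield a VO2max label, and the error rate of the three criteria together has not been worked out.
- How the analysis accounts for the label is unstated and may be settled in a statistical analysis plan that is not shown. Harm to a fitness comparison is therefore possible but not established.

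**Conclusion.** The point holds, and it is minor. As printed, the heart-rate criterion has an upper limit of 205.9 beats/min at age 18 falling to 200.8 at age 25, and exceeding it turns a test that is otherwise VO2max into VO2peak. The band follows from the protocol alone. The frequency does not: about 2% to 20% of maximal tests miss the criterion on the high side if the SD around the prediction is 5 to 12 beats/min, with normal errors centred on zero. The share mislabelled for that reason alone is lower by an amount the documents do not determine.

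The consequence is confined to a label on cardiorespiratory fitness. Measured oxygen uptake is unchanged, and brown adipose tissue activity and mass are not touched. The plateau limit merits a remark only: a slow steady rise can meet it, but whether this trial's test rises slowly enough cannot be told from the protocol.

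**What to change.** State the heart-rate criterion one-sided: peak heart rate no more than 10 beats/min below 209 − 0.73 × age, with no upper limit. Apply it in the same way at baseline and weeks 8, 16 and 25. If any tests have already been labelled with an upper limit, reassign those labels from the recorded peak heart rates.

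The cost is one reworded phrase and, at most, a recoding of one variable; no participant needs retesting. No replacement plateau rule is proposed. It would help to state whether the 100 ml/min limit spans 20 or 30 s and how fast oxygen uptake is expected to rise, so that a reader can judge whether the limit detects a plateau.

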## METHODS

The present study is a RCT (ClinicalTrials.gov ID: NCT02365129). The Human Research Ethics Committee of both University of Granada (n° 924) and *Servicio Andaluz de Salud (Centro de Granada, CEI-Granada)* approved the study design, study protocols and informed consent procedure. All participants will have to provide a written informed consent. Participants will be randomly allocated to the usual care (control), moderate-intensity exercise or vigorous-intensity exercise groups, and will be followed for 6 months during the exercise interventions. All the baseline and follow-up examinations will be performed in the same setting [*Instituto Mixto Deporte y Salud (iMUDS)* at the University of Granada and *Hospital Universitario Virgen de las Nieves, Granada, Spain*] and by the same investigators. The study will be performed following the ethical guidelines of the Declaration of Helsinki, last modified in 2013.

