### Randomization and blinding

Eligible participants will be randomly assigned after completing the baseline measurements to either the control or exercise training groups. The randomization will be computer generated. Assessment staff will be blinded to participant randomisation assignment. Participants will be explicitly informed on the group to which they will be assigned as well as on the study hypotheses and will be reminded frequently not to disclose their randomisation assignments to assessment staff in the follow-up measurements. For practical and feasibility reasons, the study will be conducted in waves of maximum 15 persons.

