**Intensity.** Several public health institutions recommend that moderate-intensity physical activity might be beneficial for health in deconditioned persons [48, 50, 51]. Yet, additional benefits have been observed of vigorous vs. moderate-intensity exercise [51]. An intensity of 60% HRres is sufficient to produce clinically significant physiological adaptations in sedentary individuals [48, 50, 51]. The intensity selected for ACTIBATE was 60% HRres for the moderate-intensity group and 80% of HRres for the vigorous-intensity group. The intensity for the resistance training will be 50% RM and 70% RM for the moderate-intensity and vigorous-intensity group, respectively. 1RM is the maximum amount of weight one can lift in a single repetition for a given exercise. An intensity equivalent to 40-50% of 1RM may be beneficial for improving muscle strength in sedentary persons beginning a resistance training program [53], whereas 60%-70% of 1RM is recommended for novice to intermediate exercisers to improve strength [53]. As the load (i.e. %RM) is not the only variable that influences strength training intensity, we will control variables as speed of movement during both concentric and eccentric phase, recovery time and range of motion. Therefore, we assume that different loads (i.e. 50% RM and 70% RM) will really constitute different training intensities [54-56].

**Frequency.** Although the physical activity recommendations suggest doing physical activity on most, preferably all days of the week, there was a concern that more than 5 days per week would be an excessive burden and might have undesirable effects on adherence and motivation to the exercise intervention program. Studies on exercise frequency show little differences for 3 or more days per week provided the weekly dose of exercise is attained [51]. Participants in ACTIBATE will be asked to do their weekly exercise dose in 3 to 4 sessions, at their own choice. The length of the training sessions will be adjusted, so that participants attending 3 or 4 days/week have the same weekly dose. Strength training will be performed on 2 of these 3 or 4 days/week, and therefore 1 or 2 sessions per week will consist solely on aerobic exercise. Participants will be advised to not to be out of training for more than 2 consecutive days, and will not be allowed to train  $<3$  days/week or  $>5$  days/week. Participants

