**Usual care group (control).** Participants randomly assigned to the usual care (control) group will receive general advices from the exercise-training specialist about the positive effects of physical activity at the start of the study. We will prepare informative pamphlets describing the benefits of physical activity that our group has prepared for the Region of Andalucía (Spain), and that meet with the World Health Organization Guidelines. [http://www.juntadeandalucia.es/salud/servicios/contenidos/andaluciaessalud/docs/130/Guia\\_Recomendaciones\\_AF.pdf](http://www.juntadeandalucia.es/salud/servicios/contenidos/andaluciaessalud/docs/130/Guia_Recomendaciones_AF.pdf).

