- **Muscular strength.** We will determine 1RM of the bench press and leg press, using the resistance weight machines (Keiser ®) that will be used in the exercise training sessions. We will also measure handgrip strength [70].

- **Appetite.** To examine whether changes in energy expenditure (REE, MIT, CIT) during and post-exercise intervention lead to increased appetite and therefore to an increased energy intake, we will assess (i) appetite through questionnaires (Three-Factor Eating Questionnaire, Binge Eating Scale, Control of Eating Questionnaire), and VAS; (ii) **Dietary intake.** It will be estimated by means of a previously validated food frequency questionnaire and 3 non-consecutive 24h dietary recalls (one weekend day and two non-weekend days). Dietary and nutritional assessment will be analysed using a database for the composition of Spanish foods. We will remind participants not to change their dietary habits.
- **Body composition.** We will also measure fat mass, lean body mass, abdominal adipose tissue and bone mineral density by conducting a DXA scan (HOLOGIC, QDR 4500W). We will also measure waist circumference.
- **Physical activity.** We will monitor unstructured daily physical activity to assess potential changes in non-supervised physical activity, and to assess non-exercise activity thermogenesis. All participants will wear two activity monitors, one on the wrist and another on the hip (ActiSleep, Actigraph, Pensacola, Florida, USA) for 7 consecutive days for 24 hours to record physical activity intensity levels and patterns, as well as sleeping habits. Participants will also complete a diary log.
- **Adverse effects.** We will record adverse effects or health problems attributable to the testing sessions or intervention sessions, including muscle pain, fatigue, and general aches and pains by self-report during the study period. An independent researcher will be in charge of auditing all assessment staff to record all these events in the participants over the study period.
- **Room and outdoor temperature.** The temperature of the exercise room as well as outdoor will be recorded all through the study from the Spanish Weather Service (*Agencia Española de Meteorología*, [www.aemet.es/es/portada](http://www.aemet.es/es/portada)). Participants will exercise at 20-22°C according to the American College of Sports Medicine [71].

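### Recording only session-attributable adverse effects makes capture asymmetric between exercise and control arms, and the recording route conflicts with assessor blinding

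*Protocol*

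**What the plan says.** The adverse-effects paragraph of the protocol (Secondary outcomes) sets the capture rule: "We will record adverse effects or health problems attributable to the testing sessions or intervention sessions". The complaints it names are non-specific ones (muscle pain, tiredness, aches), and they are taken from what participants themselves report. On who handles them, the paragraph goes on: "An independent researcher will be in charge of auditing all assessment staff to record all these events in the participants over the study period".

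Table 2 lists side effects under its secondary-outcomes heading, at baseline and weeks 4, 8, 12, 16, 20 and 25. The Statistical analysis section tests secondary outcomes by time-by-group interaction. It describes no separate comparison of adverse effects.

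On blinding, Randomization and blinding says: "Assessment staff will be blinded to participant randomisation assignment". Participants know their group and the study hypotheses, and are to be "reminded frequently not to disclose their randomisation assignments to assessment staff in the follow-up measurements".

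On exposure, exercise participants train three to four times a week: "Participants in ACTIBATE will be asked to do their weekly exercise dose in 3 to 4 sessions, at their own choice". The usual care paragraph (under Training sessions) says controls "will receive general advices from the exercise-training specialist about the positive effects of physical activity at the start of the study", plus pamphlets. No arm is exempted from testing: METHODS says "All the baseline and follow-up examinations will be performed in the same setting", and Table 2 has no arm-specific schedule.

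**The concern.** Whether an event enters the record depends on a judgement that it was caused by a session, and one of the two qualifying kinds of session exists only in the exercise arms. The named complaints (muscle pain, fatigue, aches) are common and non-specific. An exerciser has a recent training session to connect them with nearly all the time; a control can connect them only with an occasional test day. Reports come from participants who know their allocation, and the protocol does not say who else, if anyone, judges attribution.

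This is a rule about data collection, so an analysis plan cannot repair it: an event that was never recorded cannot be recovered. At stake is whether the trial can say how harms under exercise compare with harms under usual care.

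The second issue is who takes the reports. If assessors write down an event that a participant links to a training session, they learn that the participant is in an exercise arm. That is what participants are repeatedly told not to disclose to them.

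**Working it through.** The protocol states no figure on this point, so there is none to reproduce. The check has three parts.

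**1. Exposure to intervention sessions.** Inputs: Figure 2 shows 24 training weeks. The prescribed frequency is 3 to 4 sessions a week (Exercise program rationale and selection of doses). The familiarization phase, weeks 1 to 4, is fixed at 3 a week (Exercise training program).

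- Minimum: 24 × 3 = 72 sessions.
- Maximum: 4 × 3 + 20 × 4 = 12 + 80 = 92 sessions.
- Control: 0.

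Testing sessions are common to all arms. All three arms can therefore supply testing-related events, but only the two exercise arms can supply intervention-related ones.

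**2. What the filter can do to a comparison (illustration).** Let q be the true risk of any event, the same in both arms. Let s and t be the shares of exercise and control events that get labelled session-attributable. Recorded risks are then q × s and q × t. The values of q, s and t are my assumptions. The arm size of 50 is the protocol's, and 35 is 50 × (1 − 0.30), from its maximum loss to follow-up of 30%. The last two columns give the probability of a two-sided Fisher p < 0.05, by exact enumeration of two binomials, when the true risks are equal.

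| q | s | t | Recorded, exercise | Recorded, control | n = 50 | n = 35 |
|---|---|---|---|---|---|---|
| 20% | 25% | 5% | 5% | 1% | 0.024 | 0.005 |
| 30% | 50% | 10% | 15% | 3% | 0.403 | 0.216 |
| 50% | 75% | 10% | 37.5% | 5% | 0.984 | 0.914 |
| 30% | 50% | 50% | 15% | 15% | 0.024 | 0.022 |

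Over all settings tried with s above t (q of 20, 30 and 50%; s/t of 25/5, 50/10 and 75/10%; n of 35 and 50), the probability ran from 0.005 to 0.984. With equal labelling (50% in both arms) it stayed between 0.013 and 0.030. The distortion thus comes from unequal labelling. Recording every event regardless of attribution removes that source.

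**3. The recording route set beside the blinding rule.**

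- Randomization and blinding: assessment staff do not know the allocation, and participants must not tell them at follow-up.
- Adverse-effects paragraph: events attributable to intervention sessions are recorded, and the auditing sentence most naturally means that assessment staff record them and an independent researcher audits.
- Table 2: side effects are collected at five time points after baseline (weeks 4, 8, 12, 16 and 20) before the week 25 measurement of the primary outcome. At weeks 8 and 16 the same table also schedules fitness and strength tests, so reports could meet assessors there. At weeks 4, 12 and 20 only side effects are listed, and the protocol does not say who collects them.

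On that natural reading the two paragraphs cannot both be followed. Such a report would identify exercise versus control, but not moderate versus vigorous.

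**The case against.** The strongest defence is that this is a safety-monitoring rule and not a plan to compare arms. The list of secondary outcomes under Outcomes measures omits adverse effects. The headings are used loosely: Table 2's secondary block includes diet and sleep, which Outcomes measures calls other variables of interest, and the Secondary outcomes section even covers room and outdoor temperature. For monitoring harms of tests and training, an attribution rule is understandable. This stands in part: no adverse-effect comparison is spelled out. But Table 2 places side effects under secondary outcomes, at seven time points with no arm-specific schedule, and the Statistical analysis section promises a group comparison for secondary outcomes.

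A reader might also infer more than the text supports:

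- **That the record is one-sided, with controls contributing nothing.** Controls undergo the same testing, which includes a maximal treadmill test, cold exposure and biopsies. The control count is zero only for intervention-related events, and that follows from the definition.
- **That allocation is exposed.** This is a risk. The auditing sentence is awkward and can be read to mean that the independent researcher makes the entries, and participants are reminded not to disclose.
- **That every side-effect visit unblinds an assessor.** Nothing says that blinded assessors collect the reports at weeks 4, 12 and 20.
- **That the primary outcome is compromised.** Shivering is judged by observation and by asking the participant, and it sets the vest temperature before PET/CT, so a path can be imagined. But the images are read independently by two nuclear medicine physicians, and the protocol does not say that they, or the staff running the shivering test, take these reports.
- **That injuries outside the centre are all missed.** Up to 15 unsupervised sessions are allowed, and injuries in them come under the rule. Medical problems arising during the project are referred for evaluation whatever their cause, although the protocol does not say that unrelated ones are recorded.

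**Conclusion.** The point holds as an asymmetry of capture and an unresolved conflict between two paragraphs. The filter can admit a complaint in an exercise arm and exclude the same complaint in control, because about 72 to 92 intervention sessions per exerciser stand against none. Any between-arm comparison of side effects would be biased towards more events with exercise, provided that exercisers attribute a larger share of their complaints to sessions than controls do. The session counts make that likely, but the protocol gives no figure for it. The size is therefore open: the illustration runs from negligible to almost certain false significance.

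The conflict with blinding rests on the natural reading of an ambiguous sentence. It creates a risk of revealing exercise versus control; no effect on the PET/CT outcome is shown. The change should be made because lost events cannot be recovered later, but the point does not by itself undermine the primary analysis.

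**What to change.** 1. Record all adverse events in all three arms, irrespective of attribution, with identical questions at the time points already in Table 2. Hold relatedness (testing session, intervention session, neither) as a separate field. Session-related harms can still be listed from that field, so the present monitoring purpose is kept.
2. Reconcile the adverse-effects paragraph with Randomization and blinding. State that existing staff other than the blinded assessors take these reports, for example the independent researcher or the training staff, and that the reports are kept from the assessors.

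Cost: a revised form and a reassigned task. Table 2 already implies up to 7 × 150 = 1,050 side-effect contacts, so none is added, but whoever takes them on needs the time. More minor, unrelated events will have to be filed. If the independent researcher collects the reports, the audit must be kept separate, because nobody should audit their own entries. If training staff collect them, the plan must say how controls, who do not attend training, are asked the same questions.
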